### Procedure for unblinding if needed {17b}

Unblinding is not applicable to this open-label trial.

## Data collection and management

### Plans for assessment and collection of outcomes {18a}

At baseline, study staff will conduct interviews to capture baseline characteristics of the study sample, including demographics; exposure assessment (relationship with case patient; timing/intensity/frequency of contact; protective measures taken during contact); medical history (comorbidities, medications, smoking) and symptoms.

To obtain specimens for viral RNA testing (primary outcome), participants will be instructed on self-collection of oropharyngeal/nasal swabs as in prior work [64, 65], for RT-PCR testing [66–68]. Specifically, participants are asked to swab the back of their tongue, followed by the throat, before inserting the swab up to 4 cm into each nostril and rotating at least twice. These instructions are also provided in a short instructional video. Specimens will be collected at baseline, day 7, day 14 and within 24 h of new symptoms. In participants who are asymptomatic, a second self-collected swab will also be collected at day 14 and combined in the same specimen vial, or a saliva specimen will be collected if swabs are not available, since having two respiratory specimens tends to increase sensitivity for the detection of respiratory viruses [69, 70]. (If a participant has an earlier swab that is PCR positive then only one swab/saliva specimen needs to be collected at day 14.) Nasopharyngeal swabs and deep respiratory samples (e.g., bronchoalveolar lavage/endotracheal tube aspirates) already done for clinical care purposes will also be collected, with biobanking of specimens not tested in real-time for future analysis.

Follow-up interviews will be conducted at days 7, 14, 35, and 90 to assess for adverse events and clinical outcomes (hospitalizations, mechanical ventilation, mortality). Symptom data will be collected using daily electronic questionnaires that will be emailed daily for days 1–14. Participants will also be provided with a thermometer with which to record their temperature daily on days 1–14.

Methods for serologic testing of COVID-19 are still in development at the time of writing, but are rapidly emerging. At the baseline visit, participants in the active arm will self-collect dried blood spots for future testing for SARS-CoV-2 serology. These specimens will only be collected for the active arm since these participants will already be obtaining a finger-prick blood sample for HIV testing. All participants will undergo venipuncture at day 35 for batch testing of SARS-CoV-2 serology at the conclusion of the study. Self-collected saliva samples at days 1, 7, and 14 will also be used for antibody detection.

At day 14, participants will be asked to complete the K10, a short ten-item scale to measure non-specific psychological distress, as part of their electronic questionnaire. This rigorously developed instrument has differentiates between community cases and non-cases of mental health disorders according to the Structured Clinical Interview for DSM-IV [45, 46]. A standard cutoff score of ≥ 16 will be used to define short-term psychological distress.

The psychological impact of COVID-19 exposure will be assessed at day 90 using the Impact of Event Scale [47], a well-characterized 15-item scale has also been used in studies of health care workers exposed to pandemic H1N1 influenza [71, 72]. This instrument, which includes a seven-item intrusion subscale and eight-item avoidance subscale, was designed to measure the longer-term impacts of stressful life events and has good internal consistency, test-rest reliability, and sensitivity to change [47]. A standard cutoff score of ≥ 26 will be used to define a traumatic stress response [48]. Additional questions related to practical and functional impacts of COVID-19 exposure and used in previous studies on the impact of the SARS epidemic will be included at this time point also [48].

Multiple time points will incorporate the EQ-5D, a standardized instrument for assessing general health status and utility scores for incorporation into health economic analyses (https://euroqol.org/eq-5d-instruments/eq-5d-5l-about/). A utility score enables comparisons across different health interventions and diseases [73].

### Plans to promote participant retention and complete follow-up {18b}

At baseline, each participant will be asked to provide multiple modes of contact (e.g., telephone numbers, email addresses), as well as two additional persons that can be contacted in case the study team has difficulty reaching the participant for follow-up visits and clinical outcome ascertainment.

Access to serial SARS-CoV-2 testing from home will be an incentive to continued trial participation. Modest compensation will be provided in the form of $40 CAD at the day 35 in-person study visit, and another $10 CAD in the form of an electronic gift card after completion of the day 90 study visit in order to cover minor study-related costs (e.g., transportation/parking) and to encourage retention.

### Data management {19}

Study staff must maintain adequate and accurate source documents upon which case report forms for each participant are based. Data will be stored in an electronic study database (REDCap), with pre-programmed range checks to promote data quality. The trial data management center (Applied Health Research Centre of St. Michael’s Hospital) will conduct remote risk-based monitoring of this trial, including centralized review of essential study documents, as well as targeted source data verification of electronic data on 10% of participants, chosen at random.

### Confidentiality {27}

Participants will be identified using two unique study identification numbers only, and no identifying data will be stored in the central study database. No identifying information will be shared beyond the immediate members of the research team at the study site where the participant is enrolled. Participating sites are responsible for keeping any identifiable information in locked locations, if in hard copy, or in password-protected files on secure servers, if in soft copy.

### Plans for collection, laboratory evaluation, and storage of biological specimens for genetic or molecular analysis in this trial/future use {33}

Any respiratory, saliva, serum, and/or plasma specimens collected from participants but not analyzed in real-time will be stored in a biobank for potential future testing related to respiratory pathogen diagnostics and inflammatory biomarkers. No genetic testing of participants is planned.

## Statistical methods

### Statistical methods for primary and secondary outcomes {20a}

The primary outcome is microbiologically confirmed SARS-CoV-2 infection, i.e., detection of viral RNA in a respiratory specimen (oropharyngeal/nasal swab, nasopharyngeal swab, sputum specimen, saliva specimen, oral swab, endotracheal aspirate, bronchoalveolar lavage specimen) by day 14. Our primary analysis will be a generalized linear mixed model (GLMM) with logit link to estimate the effect of LPV/r on the probability of infection while accounting for clustering of participants in rings, with stratification by the randomizing site. The primary analysis will be unadjusted; in addition, multivariable models will adjust for key characteristics of both contacts (age, sex, co-morbidity, exposure characteristics such as type, duration, and timing) and index cases (illness severity, concomitant medications, etc.). In particular, we will include sex/gender-based analyses with variables specific to contacts and types of exposures. Participants with specimens positive for SARS-CoV-2 at baseline will be permitted to continue in the trial and follow all study procedures, including completion of the 14-day course of study drug for those in the active arm, as noted in section 12.2.2. These participants will be excluded from the primary and secondary analyses regarding LPV/r as PEP, but included in secondary analyses regarding early LPV/r treatment, as noted below.

To assess safety, adverse events will be tabulated according to grade and causality assessment using definitions from the DAIDS Table for Grading the Severity of Adverse Events [28], and compared between study arms.

As for the primary analysis outlined above, GLMM with logit link (for dichotomous outcomes) or identity link (for continuous outcomes) will also be used to compare the following secondary outcomes between study arms:

Symptomatic COVID-19 disease by day 14Seropositivity by day 35Days of hospitalization attributable to COVID-19 disease by day 90Respiratory failure attributable to COVID-19 disease requiring (i) non-invasive and (ii) invasive ventilation by day 90Mortality attributable to COVID-19 diseaseShort-term psychological distress, defined as scoring ≥ 16 on the K10 [45, 46] at day 14Long-term traumatic stress response, defined as scoring ≥ 26 on the IES scale [47, 48] at day 90Health-related quality of life, measured by the EQ-5D-5 L on days 1, 14, 35, and 90

Additional secondary analyses will examine the role of LPV/r in early treatment of COVID-19, in the subset of participants whose baseline specimens test positive for SARS-CoV-2. GLMM models will be used to compare the same secondary outcome measures described above.

Key transmission-related epidemiologic parameters among exposed contacts including exposure histories, cluster size, secondary attack rate (p_0_, incidence proportion), time to first viral shedding will be analyzed using descriptive statistics. Risk factors for transmission and correlates of symptomatic disease will be analyzed using logistic regression models.

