### Intervention description {11a}

The intervention is a 14-day course of LPV/r 400/100 mg (administered as two 200/50 mg tablets) orally twice daily, to be initiated as soon as possible and no later than 8 days after the latest exposure to the index case. Individuals 6 months of age and older who are unable to swallow tablets will be administered the liquid formulation of LPV/r, at equivalent weight-based dosing according to the product monograph [37]. The 14-day duration is based on COVID-19’s estimated incubation period of 6.4 days (95% credible interval = 5.6–7.7) [38], with a maximum expected incubation period similar to SARS/MERS at 14 days [39, 40].

This dosing regimen was selected based on extensive clinical experience in the setting of HIV treatment and prevention. Of note, in the setting of HIV treatment, an alternative dosing strategy of 800/200 mg once daily has been evaluated and shown to be non-inferior to twice daily dosing for that indication [41]. However, because the pharmacodynamics for LPV/r’s potential antiviral activity against SARS-CoV-2 are not fully understood, this trial will recommend twice daily dosing.

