### Participant timeline {13}

Potential participants are screened for study eligibility by telephone ± video link; consenting individuals undergo a remote (via video-link or, if not feasible, by telephone) baseline visit (day 1) within 24 h. Subsequent remote visits occur on days 7, 14, and 90; a single in-person visit is requested at day 35 to draw blood. The full schedule of events is shown in Table 1.

**Table 1 Tab1:** Schedule of events for the CORIPREV-LR trial

Visit	Screening (day 0)	Baseline (day 1)	Day 7, ± 2 days	Day 14, ± 2 days	Day 35, ± 4 days	Day 90, ± 2 days
**Visit format**	**Remote**	**Remote**	**Remote**	**Remote**	**In person**	**Remote**
Eligibility assessment	X					
Informed consent/assent	X					
Cluster randomization	X^a^					
Dispensation of study drug (LPV/r arm)		X				
Interview by study staff		X	X	X	X	X
Concomitant medication assessment		X	X	X	X	X
Adverse event assessment			X	X	X	X
Adherence diary (LPV/r arm)		Daily on d1–14				
Symptom diary		Daily on d2–15, then d21, d28, d35				
Temperature diary		Daily on d1–14				
Visit-specific questionnaire^b^		X		X	X	X
HIV self-test^c^		X				
Self-collected saliva sample		X	X	X	X	
Self-collected oropharyngeal/nasal swab^d^		X	X	X		
Self-collected dried blood spot		X^e^		X^f^		
Blood for SARS-CoV-2 serology		X^g^			X	
Stored blood samples					X	
Blood for CBC					X^f^	

^a^Randomization of the cluster occurs once all exposed contacts of an index COVID-19 case have provided their decision about study participation, or could not be contacted within 24 h of the study team becoming aware of the index case; once randomization has been completed then site coordinators should contact individual participants to conduct the baseline activities

^b^Specific components of each visit-specific questionnaire are listed in sections 13.3–13.7 below. Questionnaires can be completed on paper or via interview if internet access is unavailable. Guardians may complete questionnaires together with minors if preferred/not feasible by the minor

^c^ The HIV Self-test should only be done in participants over the age of 18 months; those under this age and those unable to perform the self-test for any reason (e.g., extreme needle phobia, limited manual dexterity) should undergo standard HIV testing at day 35 (HIV RNA test in those aged < 18 months; 4th generation antibody/antigen test for all others)

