### Concealment mechanism {16b}

Randomization will be implemented using a secure interactive web-based response system (Research Electronic Data Capture, REDCap). To ensure allocation concealment, the randomization sequence is fully concealed, and treatment assignment will not be revealed until the moment of randomization. Study personnel will then notify participants about their assigned study arm at the time of the baseline visit.

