### Implementation {16c}

The allocation sequence was generated by a statistician not otherwise involved in the trial, using a computer-generated sequence of random numbers. That statistician is the only person who will have access to the study codes. When interim analyses are conducted, only the codes related to the participants to be included in the interim analysis will be released to the biostatistician from the Data Safety and Monitoring Committee.

Study coordinators will use the web-based system to randomize rings of participants. An automated audit trail will record the time, date, allocation, and participant identification numbers. Each ring will only be randomized once all members of a ring either: give preliminary consent, decline or are classified as not contactable within the 24 h window for obtaining consent. It is essential to secure preliminary consent of the individual participants in a ring before randomization of the cluster in order to avoid selection bias, since this study is open-label.

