## Assignment of interventions: blinding

### Who will be blinded {17a}

This trial is open-label at the level of the participant, study coordinator, and investigator due to the impracticality of securing a supply of placebo. However the primary outcome is an objective biological event (microbiologic evidence of virus by RT-PCR), and lab technologists and statisticians will be blinded through the use of a randomly generated secondary participant identification number that is unlinked to cluster.

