### Methods for additional analyses (e.g., subgroup analyses) {20b}

Subgroup analyses of the primary outcome will be performed according to the type of exposed contact (e.g., healthcare workers, household members) since prior data have suggested considerably different secondary attack rates for respiratory viruses in these settings; according to the number of days between exposure and enrollment, since PEP is most likely to be effective when started as soon as possible after exposure; and according to site/city, since small differences related to practice patterns and other unknown factors may exist.

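### Exposure history used in the adjusted models and exposure subgroups is recorded after randomisation, by unblinded staff, at the visit where the participant learns the arm

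*Protocol article*

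**What the plan says.** Use of the data. The primary analysis is unadjusted, but section {20a} adds that "multivariable models will adjust for key characteristics of both contacts (age, sex, co-morbidity, exposure characteristics such as type, duration, and timing". Section {20b} plans subgroup analyses of the primary outcome by type of contact and "according to the number of days between exposure and enrollment".

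Collection of the data. Under section {18a}, the staff interview at baseline includes the "exposure assessment (relationship with case patient; timing/intensity/frequency of contact; protective measures taken during contact". Table 1 in section {13} has a staff interview on day 1 and none at screening.

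Order of events. Table 1 puts eligibility, consent and cluster randomisation on day 0. Its note a says that "once randomization has been completed then site coordinators should contact individual participants to conduct the baseline activities". Section {16c} says: "Study coordinators will use the web-based system to randomize rings of participants". Section {16b} says: "Study personnel will then notify participants about their assigned study arm at the time of the baseline visit". Section {17a} says: "This trial is open-label at the level of the participant, study coordinator, and investigator due to the impracticality of securing a supply of placebo".

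**The concern.** A covariate or subgroup factor is safe in a randomised comparison when allocation cannot have influenced its recorded value. Here the items are recalled, partly a matter of judgement, and written down after allocation by staff who can know the arm, from a participant who may just have been told it. If one arm recalls or records closer or more recent contact than the other, participants with the same recorded exposure no longer have the same underlying risk in the two arms. Adjusting for that record, or splitting by it, can then create or hide a difference.

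At stake are the adjusted estimates and the exposure subgroups. The subgroup by days since exposure matters most for interpretation, because section {20b} expects prophylaxis to work best when started early, and a spurious gradient there could be read as support for that expectation.

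**Working it through.** **1. Sequence.** Day 0: eligibility, preliminary consent, and randomisation of the ring by coordinators ({13}, {16c}). Day 1: coordinators contact participants, the arm is disclosed, the exposure interview is held and drug is dispensed (Table 1 with note a, {16b}, {18a}). The article does not say that the interview comes before disclosure. Even if it did, the interviewer could already know the arm.

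**2. What day 0 must already establish.** The first inclusion criterion in {10} requires a contact in the past 1–7 days, of a listed high-risk type, without consistent use of protective equipment. Some of type, timing and protection is therefore known before randomisation. Intensity and frequency appear only in the day-1 interview. Duration enters eligibility only as a one-hour threshold for one type of contact. Neither {20a} nor {20b} says which record feeds the analysis.

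**3. Plan figures.** No planned figure is in dispute. The sample size reproduces: 460 per arm for 15% versus 9%, times a design effect of 1 + 4 × 0.05 = 1.2, divided by 5, gives 110.4 clusters per arm against 110 stated. Nothing below changes it.

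**4. Illustration with a two-level exposure.** From the plan: control risk 15%. Assumed: half of contacts truly high-exposure, exposure odds ratio 3, no drug effect, sensitivity and specificity of the record 0.90 in controls, and specificity 0.80 on LPV/r.
- Solve 0.5·r0 + 0.5·r1 = 0.15 with odds(r1) = 3 × odds(r0): r0 = 0.0841, r1 = 0.2159.
- Risk among recorded-high = (Se·r1 + (1−Sp)·r0) / (Se + 1 − Sp). Controls: (0.9 × 0.2159 + 0.1 × 0.0841) / 1.0 = 0.2027. LPV/r: (0.9 × 0.2159 + 0.2 × 0.0841) / 1.1 = 0.192. Odds ratio 0.93.
- Risk among recorded-low = ((1−Se)·r1 + Sp·r0) / (1 − Se + Sp). Controls: 0.0973. LPV/r: 0.0987. Odds ratio 1.02.
- Logistic model with arm and recorded exposure: adjusted odds ratio 0.96. Unadjusted: 0.15 in both arms, odds ratio 1.00.

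Over assumed exposure odds ratios of 2 to 4, with controls at 0.90/0.90 and no drug effect:

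| Record on LPV/r (Se / Sp) | Unadjusted OR | Adjusted OR | Subgroup ORs |
|---|---|---|---|
| 0.90 / 0.90 (same as control) | 1.00 | 1.00 | 1.00 |
| 0.90 / 0.80 | 1.00 | 0.95–0.98 | 0.92–1.02 |
| 0.95 / 0.70 | 1.00 | 0.89–0.94 | 0.87–0.97 |
| 0.80 / 0.90 | 1.00 | 1.03–1.05 | 0.99–1.17 |

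**5. Illustration for days since exposure.** Assumed: half of contacts late, risk 15% if early and 5–8% if late, no drug effect, and a share f = 0.1–0.3 of late contacts recorded as early in one arm only.
- Misrecording on LPV/r: early-subgroup relative risk = [(0.5 × 0.15 + 0.5·f·r_late) / (0.5 + 0.5·f)] / 0.15. With f = 0.1 and r_late = 0.08: (0.079 / 0.55) / 0.15 = 0.958. With f = 0.3 and r_late = 0.05: (0.0825 / 0.65) / 0.15 = 0.846.
- The same misrecording in controls instead: 1 / 0.958 = 1.04 to 1 / 0.846 = 1.18.

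The sign depends on which arm misrecords, and the documents do not settle that.

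**The case against.** The strongest reply is that eligibility already fixes the essentials before randomisation. Days since exposure could come from that record, and a relationship such as household member or healthcare worker is factual and hard to shift by arm. This stands in part. It narrows the items at risk and makes the remedy easy, but the article does not say that the day-0 record is the analysis source, and it lists the exposure assessment under the day-1 interview.

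A second reply is that the order of forms within a visit belongs to the full protocol, and that disclosure at the baseline visit could follow the interview. That is possible. However, the article itself fixes randomisation before the interview and leaves coordinators unblinded, and an analysis plan cannot make day-1 answers free of the arm afterwards.

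Four stronger readings are tempting and are not supported:
- **Day-1 EQ-5D-5L as a biased covariate.** It appears only as one time point of an outcome, with main interest at day 14 ({12}, {20a}). No adjustment, subgroup or risk-factor use is planned.
- **Risk-factor models distorting the treatment comparison.** The article lists no predictors for them, and they do not compare arms.
- **A built-in incentive on LPV/r to restate dates.** Drug is to start "no later than 8 days after the latest exposure to the index case". Eligibility at 7 days or less plus a baseline visit within 24 h gives at most 7 + 1 = 8 days, so the limit would normally exclude nobody.
- **Bias towards benefit.** This needs misrecording in one arm and one direction, which nothing in the article supports.

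**Conclusion.** The point holds for the detailed exposure history and for the analyses that use it: the adjusted models and the subgroups by contact type and days since exposure. Age, sex and the site subgroup are hardly affected. The unadjusted primary analysis does not use these variables, and its outcome is a PCR result read by blinded laboratory staff.

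The bias is possible, not shown. Its direction is open and its size unknown. The ranges above (adjusted odds ratio about 0.89–1.05, exposure-subgroup odds ratios about 0.87–1.17 under no effect) rest wholly on assumed misreporting rates, exposure prevalence and exposure effects. If reporting is equally accurate in both arms, the bias is nil. The weakness is worth correcting because these analyses are planned and the correction is cheap, but it does not threaten the main conclusion.

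**What to change.** - In {13} and {18a}, record exposure dates, type, duration and protective measures at the day-0 eligibility contact, and lock them in REDCap before the ring can be randomised. REDCap already runs the randomisation.
- Complete any remaining exposure detail and the first EQ-5D-5L before the arm is revealed to the participant. This protects the participant's answers but not against an interviewer who knows the arm, so such detail should not replace the locked values.
- State in {20a} and {20b} that the adjusted models and exposure subgroups use the pre-randomisation values.
- For participants already enrolled, use the day-0 eligibility record where available. Where it lacks an item, report that the value was recorded after allocation.

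The cost is a few more minutes on the day-0 call, inside the 24 h window for reaching contacts, plus a change to the REDCap form order and a sentence in the analysis section. No visit, participant or sample is added and the sample size is unchanged. Comorbidity, symptoms and the full set of questionnaires need not move to day 0.
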